## Abstract

**Background:**

This multicenter, double-blinded, randomized controlled trial (RCT) aims to assess the impact of an artificial intelligence (AI)-based model on the efficacy of intracranial aneurysm detection in CT angiography (CTA) and its influence on patients’ short-term and long-term outcomes.

**Methods:**

*Study*
*design*: Prospective, multicenter, double-blinded RCT.

*Settings*: The model was designed for the automatic detection of intracranial aneurysms from original CTA images.

*Participants*: Adult inpatients and outpatients who are scheduled for head CTA scanning.

Randomization groups:

(1) Experimental Group: Head CTA interpreted by radiologists with the assistance of the True-AI-integrated intracranial aneurysm diagnosis strategy (True-AI arm).

(2) Control Group: Head CTA interpreted by radiologists with the assistance of the Sham-AI-integrated intracranial aneurysm diagnosis strategy (Sham-AI arm).

*Randomization*: Block randomization, stratified by center, gender, and age group.

*Primary outcomes:* Coprimary outcomes of superiority in patient-level sensitivity and noninferiority in specificity for the True-AI arm to the Sham-AI arm in intracranial aneurysms.

*Secondary outcomes:* Diagnostic performance for other intracranial lesions, detection rates, workload of CTA interpretation, resource utilization, treatment-related clinical events, aneurysm-related events, quality of life, and cost-effectiveness analysis.

*Blinding:* Study participants and participating radiologists will be blinded to the intervention.

*Sample size*: Based on our pilot study, the patient-level sensitivity is assumed to be 0.65 for the Sham-AI arm and 0.75 for the True-AI arm, with specificities of 0.90 and 0.88, respectively. The prevalence of intracranial aneurysms for patients undergoing head CTA in the hospital is approximately 12%. To establish superiority in sensitivity and noninferiority in specificity with a margin of 5% using a one-sided *α* = 0.025 to ensure that the power of coprimary endpoint testing reached 0.80 and a 5% attrition rate, the sample size was determined to be 6450 in a 1:1 allocation to True-AI or Sham-AI arm.

**Discussion:**

The study will determine the precise impact of the AI system on the detection performance for intracranial aneurysms in a double-blinded design and following the real-world effects on patients’ short-term and long-term outcomes.

**Trial registration:**

This trial has been registered with the NIH, U.S. National Library of Medicine at ClinicalTrials.gov, ID: NCT06118840. Registered 11 November 2023.

**Supplementary Information:**

The online version contains supplementary material available at 10.1186/s13063-024-08184-9.

## Introduction

Artificial intelligence (AI) has had a tremendous influence on the interpretation of medical images [1], such as the diagnosis of intracranial aneurysms in CT angiography (CTA), which is the first-line imaging examination [2–4]. In routine clinical practice, radiologists often misdiagnose intracranial aneurysms due to their small size, complexity of intracranial vasculature [5], and heavy workload [6], which may impose risk for patients with intracranial aneurysms, which can cause nontraumatic subarachnoid hemorrhage (SAH) with a high rate of mortality and disability [7–9]. AI has demonstrated improved reader performance on limited retrospective datasets [10–13], while critics point out that AI systems may be less helpful than retrospective data would suggest and almost all previous AI studies were performed in an open-label design (comparing “AI + readers” vs AI alone or readers alone), which would introduce Hawthorne effect and automation biases [14–16]. There is a lack of high-level evidence for the real-world evaluation of AI systems, especially prospective, real-world, double-blinded randomized controlled trials (RCTs), which are the highest standard evidence in this field.

Moreover, there is still a lack of relevant researches on the impact of AI on the consequent clinical practice and patient outcomes [17, 18]. Accuracy alone is not enough to determine clinical utility because the information gained from diagnostic testing does not have a direct effect on patient outcomes [19]. Recently, Kim and colleagues found that, compared with the AI model, nearly 90% of the aneurysms missed in the clinical radiology report while detected by AI received no further reference; of the aneurysms detected by clinical radiology report, 42.3% underwent further clinical management [20]. Apparently, accurate diagnosis of intracranial aneurysms would alert clinical teams and patients themselves; therefore, it would facilitate patients’ subsequent care downstream in clinical care [21]. To build trust in medical AI systems, demonstrations of impact on clinical outcomes are highly recommended for AI systems, otherwise resulting in widespread doubts about its real effect [16, 22].

Therefore, by introducing Sham-AI as the placebo control ([name], [name], [name], [name], [name], [name], [name], [name], [name], [name], et al: Propose and validation of a placebo control for AI models in intracranial aneurysms detection: a Multi-centre, Multi-reader, Blinded Crossover Study, unpublished), we designed this prospective, multicenter, double-blinded RCT with two parallel groups and a 1:1 allocation to the True-AI or Sham-AI arm to more rigorously evaluate the hypothesis that a deep-learning-based model for intracranial aneurysm detection in CTA would improve radiologists’ diagnostic performances (the superiority of sensitivity and noninferiority of specificity (a noninferiority margin of 5%) for the intervention group to the control group) and explore patients’ outcomes in the real world to provide the highest level of medical evidence for the clinical deployment of AI systems.

## Methods/design

### Study design

This is a prospective, parallel-group, multicenter, double-blind RCT to investigate the impact of a deep-learning-based computer-aided diagnosis strategy for intracranial aneurysms on the diagnostic performances of radiologists and short-term and long-term outcomes of adult inpatients and outpatients between True-AI and Sham-AI group in a real-world setting. By implementing True-AI and Sham-AI and utilizing randomization, the double-blinded approach is employed to neutralize the subjective influence of participation in an AI trial on diagnostic performance.

The study is being conducted in 25 large-scale, tertiary care hospitals located in 10 provinces across China. Participants will be recruited and randomized into either the experimental or control groups in a 1:1 ratio in each site. In the experimental group, head CTA images will be interpreted by radiologists with True-AI-integrated intracranial aneurysm diagnosis strategy (True-AI arm), which had a patient-level sensitivity of 0.93 in the validation dataset ([name], [name], [name], [name], [name], [name], [name], [name], [name], [name], et al: Propose and validation of a placebo control for AI models in intracranial aneurysms detection: a Multi-centre, Multi-reader, Blinded Crossover Study, unpublished). In the control group, CTA will be interpreted by radiologists with a Sham-AI-integrated intracranial aneurysm diagnosis strategy (Sham-AI arm), which had a patient-level sensitivity of 0.02 in the same validation dataset, which is close to zero and would not help radiologists detect any aneurysms while expose the radiologists to the same incidental effects of the Standard-AI ([name], [name], [name], [name], [name], [name], [name], [name], [name], [name], et al: Propose and validation of a placebo control for AI models in intracranial aneurysms detection: a Multi-centre, Multi-reader, Blinded Crossover Study, unpublished) [23]. The study design is illustrated in Fig. 1. This study protocol is reported according to the Standard Protocol Items: Recommendations for Interventional Trials-Artificial Intelligence (SPIRIT-AI) [24]. The SPIRIT-AI Checklist is provided in the Supplementary materials. Table 1 shows the SPIRIT-AI schedule for patient enrollment, intervention, and assessment.

**Fig. 1 Fig1:**
[figure not shown]
Randomization and follow-up of the patients. *Study reports lost is defined as those whose CTA exams were accidentally interpreted by other radiologists not involved in the trial. AI = artificial intelligence, CTA = CT angiography, mRS = Modified Rankin Scale

**Table 1 Tab1:** The SPIRIT-AI schedule of enrollment, interventions, and assessments

	STUDY PERIOD				
	Enrollment	Allocation	Assessments	3-month Follow-up	12-month Follow-up
TIMEPOINT	t1	t2	t3	t4	t5
ENROLLMENT					
Inclusion and exclusion criteria assessment	X				
Informed consent	X				
Allocation to participating radiologists	X				
CTA examination	X				
Randomization	X				
Baseline information collection	X				
INTERVENTION:					
True-AI-integrated diagnosis		X			
Sham-AI-integrate diagnosis		X			
ASSESSMENTS:					
Groundtruth diagnosis			X		
Diagnostic performance assessment			X		
Work load			X		
Resource use				X	X
Treatment-related clinical events				X	X
Life quality evaluation				X	X
Outcomes of aneurysm-related events				X	X
Cost-effectiveness analysis				X	X

*AI* artificial intelligence, *CTA* CT angiography, *MRA* magnetic resonance angiography, *SPIRIT-AI* standard protocol items: recommendations for interventional trials-artificial intelligence

### Participating center qualification

The 25 medical centers are located in 7 different geographical regions of China (North China, Northeast China, East China, Central China, South China, Southwest China, Northwest China). Each center is a tertiary care hospital and has experience in the diagnosis of intracranial aneurysms, with an average of 250 patients undergoing head CTA examination each month. Thus, the cohort can adequately represent the population at the regional and national levels. These centers are needed to shut down other AI-based intracranial aneurysm detection models until patient enrollment is completed.

### Participants and recruitment

Participants who fulfil the following criteria will be eligible:

Inclusion criteria:Adult inpatients and outpatients who are scheduled for head CTA scanning.

Exclusion criteria:Age under 18 years;Patients with contraindications to CTA;Modified Rankin Scale (mRS) score > 3;Refusal to sign informed consent;Participation in other clinical studies of intracranial aneurysms;Patients with failed head CTA scanning or incomplete image data or poor image quality.

### Interventions

#### Procedures

Eligible patients will be invited to participate in a clinical trial involving the use of an AI-integrated intracranial aneurysm detection strategy by a local staff member, with the option to opt-out if they wish, and will undergo a conventional path without AI assistance (not included in the study population). Written informed consent will be obtained from all participants who agree and wish to take part in the study. Details of case recruitment and study withdrawal are provided in the Supplementary Appendix. Directly after a participant has undergone head CTA scan, the CTA image series will be automatically caught by an onsite hospital-based workstation (DeepWise Aneurysm Aided Detection Software, v1.0.0.2, DeepWise, Beijing, China). Subsequently, the case will be randomized and allocated to either the intervention (True-AI) or control (Sham-AI) arm in a 1:1 ratio, with a pseudorandom number assigned within the workstation. The Sham-AI model can effectively mimic the True-AI model and does not assist doctors in detecting any aneurysms, essentially acting as a placebo (Fig. 2). CTA will be interpreted by radiologists with the assistance of either True-AI or Sham-AI, as part of the study.

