**Fig. 2 Fig2:**
[figure not shown]
Procedures of patient enrollment and randomization. AI = artificial intelligence, CTA = CT angiography, mRS = Modified Rankin Scale

The AI-processed image series provided suggestions for suspected intracranial aneurysms, and the radiologists could accept or reject the suggestions according to their own judgment. Both True-AI and Sham-AI can be displayed in an identical human-AI interaction platform.

Each center includes at least two participating radiologists, junior radiologists (usually attending radiologists) writing the initial report, and senior radiologists reviewing and releasing the report, which is the standard of care in China and the radiology community [25]. The participating radiologists need to meet the predefined requirements and been trained for diagnosis of intracranial aneurysms. They will assess the quality of images and data availability. In both study groups, the junior radiologists will interpret CTA images firstly without AI assistance; if aneurysms are diagnosed by junior radiologist, he/she is required to input the three-dimensional coordination of each diagnosed aneurysm in the study website.

Then the AI system act as a second reader, and will judge whether the radiologist’s diagnosis is overlapped with the AI suggestions according to the three-dimensional coordination, and only present AI suggestions that are not overlapped with radiologist’s diagnosis on the study website (the radiologist will not have access to the original AI predictions except for the presenting results). The junior radiologist will continue to independently re-assess the additional suggestions, and potentially modify his/her initial judgment accordingly, to determine his/her final report (Fig. 3). The senior radiologist has access to the first reader’s assessment and will review and release the official radiological report. They can assign cases to a consensus meeting when the radiologists find a case difficult or equivocal, where the case will be discussed at their local site for a final decision. After the diagnosis is made, the patients will be treated according to national and institutional guidelines. The requirements for participation, adherence, and protocol deviations and study monitoring are provided in the Supplementary Appendix.

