#### Data analysis plan

The intention-to-treat (ITT) population will include all patients who are randomized while exclude those who withdrew consent; modified ITT (mITT) population will exclude those whose CTA are not interpreted by the study radiologists, and those with the corresponding AI process failing, and those who withdrew consent; while the Per-protocol (PP) population will only include patients who receive the randomized treatment and do not exhibit major protocol violations, excluding (1) those who withdrew consent; (2) those whose CTA are not interpreted by the study radiologists; (3) those with the corresponding AI process failing; (4) those with the participating radiologists chose not to review AI suggestions, which will be recorded by the background record.

The hypothesis of the study is that the patient-level sensitivity in the intervention arm is superior to that in the control arm, and the patient-level specificity is noninferiority, with a noninferiority margin of 5%. A comparison between the experimental group and the control group for the two primary outcomes will be conducted using the chi-square test or Fisher’s exact test. The results will include the *p* value (2-sided) and the ratio of patient-level sensitivity and specificity. The primary analysis will be based on the ITT population.

Continuous variables will be reported as the means with standard deviations (SDs) or medians with interquartile ranges (IQRs), depending on their distributions. Categorical variables will be presented as numbers and percentages. Statistical significance was set at *p* < 0.05. A 95% CI will be calculated using the Clopper-Pearson method.

The following subgroups will be included:Centers (25 centers), provinces (10 provinces), geographical areas and physician working experiences (working experiences of < 10 years vs. ≥ 10 years) and physician level (junior radiologists vs senior radiologists).Size (< 5 mm vs. ≥ 5 mm) and locations of intracranial aneurysms (anterior vs posterior, internal carotid artery vs. middle cerebral artery vs. anterior cerebral artery vs. posterior communication artery vs. anterior communication artery vs. vertebral basilar artery vs. others).Gender of patients (male vs. female), age (≤ 54 years or. > 54 years), SAH status (with vs. without SAH).History of head DSA or surgery (yes vs. no).Subsequent head DSA or surgery (yes vs. no).

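### Drawing the allocation at image capture, before the arms can differ, lets scans that never meet AI into the primary ITT set; drawing it when the unaided read is submitted is a cheap improvement

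*Protocol article*

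**What the plan says.** **Order of events.** The Procedures section states: "Directly after a participant has undergone head CTA scan, the CTA image series will be automatically caught by an onsite hospital-based workstation". It continues: "Subsequently, the case will be randomized and allocated to either the intervention (True-AI) or control (Sham-AI) arm in a 1:1 ratio". The Blinding section confirms that the draw is automatic once the examination has been acquired, and Table 1 lists randomisation in the enrolment column. The text after Fig. 2 then says: "In both study groups, the junior radiologists will interpret CTA images firstly without AI assistance". AI suggestions that do not overlap the junior's findings appear only after that read has been entered.

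**Analysis sets.** The Data analysis plan states: "The intention-to-treat (ITT) population will include all patients who are randomized while exclude those who withdrew consent". In contrast, the "modified ITT (mITT) population will exclude those whose CTA are not interpreted by the study radiologists, and those with the corresponding AI process failing". The per-protocol set also drops "those with the participating radiologists chose not to review AI suggestions, which will be recorded by the background record". On the primary set: "The primary analysis will be based on the ITT population". No role in the noninferiority decision is stated for the other two sets.

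**Scans read outside the trial.** The Fig. 1 legend and the closing paragraph of the Data analysis plan call these lost study reports. The latter lists them as potential missing data.

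**Sample size.** The 5% attrition allowance is attributed to withdrawal of consent. Joint power at 6450 is given as 0.800.

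**The concern.** Between capture and the submitted unaided read, a scan can go to a radiologist outside the trial or the AI can fail on it. The protocol foresees both events. Because the draw comes first, such scans already belong to an arm, and the ITT definition keeps them although they never met the thing being compared.

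Scans like these have the same expected result in both arms and pull both differences toward zero. For sensitivity, a superiority question, that costs power. For specificity, a noninferiority question, it works in the trial's favour: a loss among exposed scans that reaches the margin looks smaller in the ITT set. The specificity endpoint is there to rule out that loss, and trial success requires both endpoints.

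**Working it through.** **Inputs (Sample size calculation).** One-sided alpha 0.025; sensitivity 0.65 and 0.75; specificity 0.90 and 0.88; margin 0.05; 774 patients with and 5676 without aneurysm at N = 6450; attrition 5%.

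**Step 1: reproduce the stated powers.**
- Sensitivity, n per arm = 774 × 0.95 / 2 = 367.65. Pooled z-test: Φ{[0.10 − 1.96·√(2·0.70·0.30/n)] / √[(0.65·0.35 + 0.75·0.25)/n]} = Φ{(0.10 − 0.0662)/0.0336} = Φ(1.005) = 0.842 (stated 0.841).
- Specificity, n per arm = 5676 / 2 = 2838. SE = √[(0.90·0.10 + 0.88·0.12)/2838] = 0.0083. Power = Φ(0.03/0.0083 − 1.96) = Φ(1.654) = 0.951 (stated 0.951).
- Joint: 0.842 × 0.951 = 0.801 (stated 0.800).

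The sensitivity figure reproduces with the 5% attrition and the specificity figure without it. I keep that basis. With attrition in both, joint power starts at 0.793 and the pattern below is the same.

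**Step 2: dilution.** Let x be the share of ITT scans with no AI exposure. The article gives no value, so x is an assumption. I take it as equal in both arms and give unexposed scans the Sham-AI rates. Then in the True-AI arm:
- sensitivity = 0.65 + 0.10(1 − x);
- specificity = 0.90 − 0.02(1 − x).

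**Step 3: noninferiority when the exposed loss equals the margin.** Specificity in True-AI is 0.90 − 0.05(1 − x), so the distance to the margin is 0.05x and the chance of passing is Φ(0.05x/SE − 1.96). At x = 5%: specificity 0.8525, SE = √[(0.09 + 0.8525·0.1475)/2838] = 0.00872, Φ(0.0025/0.00872 − 1.96) = Φ(−1.673) = 0.047.

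**Step 4: the alternative.** If the same scans are not randomised and the number consented stays fixed, the full effect applies to n(1 − x).

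| x (assumed) | Sensitivity power, ITT | Specificity power, ITT | Joint power, ITT | Joint power, not randomised, same number consented | Chance of passing noninferiority, exposed loss = 5 points |
|---|---|---|---|---|---|
| 0 | 0.842 | 0.951 | 0.801 | 0.801 | 2.5% |
| 2% | 0.827 | 0.956 | 0.790 | 0.791 | 3.2% |
| 5% | 0.802 | 0.963 | 0.772 | 0.775 | 4.7% |
| 10% | 0.756 | 0.972 | 0.735 | 0.746 | 8.3% |

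**Step 5: patients to consent for 6450 randomised.** 6450/(1 − x) gives 6582, 6790 and 7167 at 2%, 5% and 10%.

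**The case against.** **Allocation after capture is a legitimate choice.** It is neither an error nor a contradiction, and ITT is conservative for superiority. This stands. The point is an improvement to the design.

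**The noninferiority error concerns a different question.** The trial compares AI-integrated strategies in routine practice. If AI failure and bypassed readings count as part of the strategy, the ITT test keeps its 2.5% level. This also stands: the raised error belongs to the effect among exposed scans. That effect still matters here, because the Discussion says the design is meant to isolate what AI itself contributes.

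**Outside-read scans may not dilute at all.** A reader might infer that they certainly do, since ITT keeps all randomised patients. The article also lists them as potential missing data and gives no rule for their outcome. If they carry none, the cost is lost sample size. Only AI-failure scans that still get a trial report dilute on the face of the text.

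**The shares may be small.** The article describes outside reads as accidental, which suggests few. Nothing in it supports 10%.

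**The mITT set already exists.** For outside reads, exclusion should not depend on arm, because the arms are identical and allocation is hidden at that stage. A reader might infer that the mITT set is biased in general; the text does not support that. The exception is failure of the corresponding AI, which is judged on a different model in each arm and so could differ between arms.

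**Conclusion.** The point holds as a modest, inexpensive improvement. The draw precedes exposure, the only primary set keeps scans the AI failed on, and the sample size allows for consent withdrawal alone. Noninferiority for the effect among exposed scans is then tested at about 3.2%, 4.7% or 8.3% in place of 2.5% if 2%, 5% or 10% of ITT scans are unexposed. Sensitivity power falls from 0.842 to 0.827, 0.802 or 0.756. At 1% to 2% the effect is small. These figures rest on assumed shares, equal shares in the two arms, and Sham-AI rates for unexposed scans.

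A reader might go further and infer that a later draw would restore the planned power with no extra patients. It would not: at a fixed number consented, joint power at 5% is 0.775 with the later draw against 0.772 without it. The gain is that noninferiority is tested at its nominal level among scans that reach the AI, with no exclusion after randomisation for these two reasons.

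**What to change.** Run both models in the background on every captured scan. Draw the allocation automatically when the participating junior submits the unaided read, immediately before any suggestion is displayed. Do not randomise a scan with no submitted trial read or on which either model failed; the failure criterion is then the same in both arms. Keep the strata and blocks. Amend the Procedures and Randomization sections and Table 1.

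**Costs.**
- A software change to the trigger, and a second model run per scan. The draw stays automatic, so concealment is unaffected.
- More patients consented to reach 6450 randomised: 132, 340 or 717 extra at 2%, 5% or 10%. Without them joint power is essentially not recovered.
- Results apply to scans on which the AI runs.

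**What it does not cure.** Scans whose suggestions the reader declines to review after the draw remain in the ITT set.

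The Trial status section says enrolment had not begun at submission. If the trigger can no longer be changed, requiring the mITT analysis to agree before noninferiority is claimed would address most of the validity issue, subject to the caveat about arm-specific AI failure.
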